##### Statistics and sample size

Data will be tested for normality and then analyzed with parametric or non-parametric procedures, as appropriate. Accordingly, univariate analysis using Student and analysis of variance or Mann-Whitney, Wilcoxon, Kruskal-Wallis and Friedman tests will be performed. Some laboratory data will be subjected to correlation analysis with clinical findings, using Pearson's, Spearman's or Kendall's technique, according to data characteristics.

Subsequently, if needed, significant results will be subjected to multiple curve estimation procedure [66] and/or multivariate analysis according to data characteristics and the results of the univariate analyses. The genetic data will be analyzed using χ^2 ^test for the Hardy-Weinberg equilibrium of alleles at the individual loci. The association between genotypes and clinical data will be tested with χ^2^- or Fisher test and then with logistic regression or analysis of co-variance, as appropriate [67]. All statistical analyses will be performed by the project coordinators, who have a long experience and formal training in biostatistics.

Despite a formal sample size calculation is not warranted, based on the available data [5,11,19], we previewed a convenience sample size, as follows: 50-60 preterm infants affected by iRDS, with at least 20 receiving a second surfactant dose; for ARDS and IRRF groups 20 patients will be also convenient, while 10 control neonates or infants will be considered. These sample size have been checked for power regarding the correlation between sPLA2 activity and two selected clinical variables (using Power and Precision demo rel. 3.2 [68]). Given α-error of 0.05 and a correlation coefficient (*r*) ≥ 0.6 and ≥ 0.85 [5,11,19] for the respiratory compliance and the PaO_2_/FiO_2 _ratio, respectively, the power resulted > 80% in both cases.

The study is supposed to last 12-18 months for the enrolment phase in each collaborating centre, and 3-6 months for the laboratory phase at the coordinating centre.

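### Between-group tests are chosen on normality, with no unequal-variance form named, for groups of 10, 20 and 50-60: if spreads differ, those comparisons do not hold their 5% level

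*Protocol article*

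**What the plan says.** All of this stands in the protocol article under Statistics and sample size.

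- Rule for the choice of test: "Data will be tested for normality and then analyzed with parametric or non-parametric procedures, as appropriate".
- Tests that follow from it: "Accordingly, univariate analysis using Student and analysis of variance or Mann-Whitney, Wilcoxon, Kruskal-Wallis and Friedman tests will be performed".
- Planned sizes: 50-60 in the iRDS group. The other sizes are given as follows: "for ARDS and IRRF groups 20 patients will be also convenient, while 10 control neonates or infants will be considered". I read the 20 as 20 in each of ARDS and IRRF. No number is given for MAS, so MAS is left out of the calculations.
- Power: "These sample size have been checked for power regarding the correlation between sPLA2 activity and two selected clinical variables". Group comparisons have no power check.

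The section gives no SDs, does not list which groups are compared, and sends only significant univariate results on to multivariate analysis.

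**The concern.** Whether a variable is normal says nothing about whether its spread is the same in each group. On the parametric branch, Student's t and ordinary ANOVA assume one common variance. On the rank branch, Mann-Whitney and Kruskal-Wallis take their null distribution from identical distributions. In both cases the hypothesis tested is equal level and equal spread together. With equal group sizes this matters little. With sizes differing up to sixfold (10 against 60) it can matter a good deal, and the direction depends on whether the smaller group is the more or the less variable one.

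Unequal spread is plausible here. The enrolment criteria define clinically very different groups, from controls with normal chest findings to late IRRF at any age. Because univariate significance decides what goes forward to multivariate modelling, a false positive is carried on and a missed difference stops there.

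The Wilcoxon and Friedman tests, if used for repeated samples in the same infant, are not touched by this point.

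**Working it through.** **1. The plan's own figure.** The article states "Given α-error of 0.05 and a correlation coefficient (*r*) ≥ 0.6 and ≥ 0.85" and "the power resulted > 80% in both cases". Fisher's z gives power = Φ(atanh(r)·√(n−3) − 1.96), two-sided 5% assumed.

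- n=20, r=0.6: 0.693 × 4.123 − 1.96 = 0.898, power 81.5%.
- n=20, r=0.85: 1.256 × 4.123 − 1.96 = 3.22, power 99.9%.

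The figure reproduces for groups of 20 or more. It concerns correlations and says nothing about group comparisons.

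**2. Why the level moves (Student).** The true variance of the difference in means is s₁²/n₁ + s₂²/n₂. Student uses sₚ²(1/n₁ + 1/n₂), where sₚ² is the pooled variance. Rejection under equal means is roughly 2Φ(−t/√(true/used)), where t is the critical value.

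- *20 v 55, smaller group with SD 2, larger with SD 1.* True: 4/20 + 1/55 = 0.218. Pooled variance: (19×4 + 54×1)/73 = 1.781. Used: 1.781 × 0.0682 = 0.121. √(0.218/0.121) = 1.34, and 2Φ(−1.993/1.34) ≈ 14%.
- *Same sizes, larger group with SD 2.* True: 1/20 + 4/55 = 0.123. Used: (19 + 216)/73 × 0.0682 = 0.219. √(0.123/0.219) = 0.75, giving about 0.8%.
- *20 v 20.* True and used are both (s₁² + s₂²)/20, so the ratio is 1 whatever the SDs.

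**3. Simulation.** Inputs: the group sizes above (55 as midpoint for iRDS), normal data, equal centres, two-sided 5%, 20,000 runs for two groups. The SD ratios are assumptions. The ratio is the smaller group's SD over the larger group's.

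| Comparison | SD ratio | Student | Mann-Whitney |
|---|---|---|---|
| 20 v 55 | 0.5 | 0.9% | 2.1% |
| 20 v 55 | 1 | 4.9% | 4.7% |
| 20 v 55 | 1.5 | 10.7% | 7.7% |
| 20 v 55 | 2 | 14.3% | 9.6% |
| 20 v 55 | 3 | 19.4% | 12.1% |
| 10 controls v 55 | 0.5 | 0.3% | 1.1% |
| 10 controls v 55 | 2 | 21.0% | 11.3% |
| 10 controls v 20 | 0.5 | 1.8% | 2.8% |
| 10 controls v 20 | 2 | 11.5% | 7.9% |
| 20 v 20 | 0.25 to 4 | 4.5-5.7% | 4.4-7.6% |

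Welch's t stays at 4.5-5.6% in every row. A repeat run that added Brunner-Munzel put it at 5.0-5.8% for ratios from 0.5 to 3.

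Three disease groups (55/20/20), the two groups of 20 more variable by 1.5 / 2 / 3: ANOVA rejects 10.4 / 13-14 / 17-18% and Kruskal-Wallis 7.9 / 9-10 / 12-13%. Welch's ANOVA stays near 5%.

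**4. Power against the 10 controls** (difference in units of the disease SD).

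| Sizes | Control SD / disease SD | Difference | Student | Mann-Whitney | Welch |
|---|---|---|---|---|---|
| 10 v 20 | 0.5 | 0.8 | 64% | 67% | 80% |
| 10 v 55 | 0.5 | 0.8 | 76-77% | 85% | 96% |
| 10 v 55 | 0.5 | 0.5 | 26% | 38% | 63% |
| 10 v 20 | 1 | 0.8 | 51% | 46% | 49% |
| 10 v 55 | 1 | 0.8 | 62% | 58% | 56% |

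**The case against.** The strongest objection is that neither the SD ratio nor its direction is in the article. That stands. The enrolment criteria can be read either way. Controls have normal lungs, but they span neonates and infants ventilated for quite different reasons. iRDS is one disease, but it covers every gestation up to 37 weeks. A reader might infer that false positives between diseases rise two- to fourfold and that power against controls is lost. The article does not support this as an unconditional statement:

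- If iRDS is the more variable group, the error falls below 5%.
- If controls are the more variable group, the trouble against them is false positives.
- The upper end of that range belongs to Student at an SD ratio of about 3 or more. The rank tests inflate about 1.5- to 2.5-fold at ratios of 1.5 to 3.
- ARDS v IRRF is hardly affected.

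Two further inferences go too far. One is that normality alone decides: the text qualifies the rule by appropriateness, so normality is the only *stated* criterion. The other is that the first two study aims rest on group comparisons: those aims are to identify subtypes and to study modulators, and no contrasts are listed.

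It can also be said that a fuller plan may settle the form of the t-test. That is possible. But this article does name its tests, and none of those for independent groups allows for unequal variance, so the point concerns a choice already stated.

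Finally, log transformation changes the question from arithmetic means to geometric means. With log-normal data of equal arithmetic means (log-SD 1.0 v 0.5, 20 v 55), Welch on logs rejects 34%, because the geometric means do differ. Logs should therefore be conditional and their target stated.

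**Conclusion.** The point holds in conditional form. With the named tests and the planned sizes, comparisons between unequal groups hold their 5% level only if spreads are about equal, and nothing in the article shows that they are. For an assumed SD ratio of 1.5-3 with the group of 20 the more variable, Student's error is about 10-20% and Mann-Whitney's about 8-13%. With iRDS twice as variable, both are about 1-2%. Against 10 controls with half the disease SD, Student gives up about 20 points of power to Welch (10 v 55, 0.8 SD). With controls twice as variable, its error is about 21%. At equal SDs, and for 20 v 20, there is no material problem.

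The case for Welch does not depend on guessing the direction, because it holds the level either way. This is an inexpensive improvement in method; it does not show that any particular result will be wrong.

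**What to change.** For comparisons between independent groups, replace Student's t and ordinary ANOVA with Welch's t-test and Welch's ANOVA, whatever the outcome of a variance check. Where assay values are skewed, apply them on the log scale and report ratios of geometric means with 95% confidence intervals, saying that this is the quantity compared. Where a rank test is needed, use Brunner-Munzel in place of Mann-Whitney. Kruskal-Wallis has the same weakness, so say what replaces it, for example pairwise Brunner-Munzel tests with a stated multiplicity adjustment.

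The change is to analysis wording only and needs no new data. If SDs are in fact equal, Welch costs about 1-2 points of power for 10 v 20 (51% to 49% at 0.8 SD) and about 5-6 points for 10 v 55 (62% to 56%).

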### sPLA2 and iRDS

The importance of surfactant is well known in neonatal critical care. An inadequate surfactant production is the pivotal cause of hyaline membrane disease, also called infant respiratory distress syndrome (iRDS), the most frequent respiratory disease of preterm infants [16]. Although exogenous surfactant administration is curative in many preterm infants, long-term respiratory sequels are still a significant problem in this population, with 20% of the surviving preterm babies affected by BPD [17]. Moreover, the tiniest babies born at the limit of viability often require multiple surfactant administrations. Many of these very preterm deliveries are associated with infections and chorioamnionitis [18]. In these cases, inflammation lengthens the lung injury, decreasing the usefulness of exogenous surfactant and damaging the lung tissue [18]. In such situation, sPLA2 is likely to play a crucial role: we found increased sPLA2 levels in babies with iRDS comparing to normal term neonates [19]. sPLA2 was found to increase foetal neutrophil migration and so to enhance lung tissue inflammation [20]. Babies with higher sPLA2 activity are likely to be the ones needing repeated surfactant administrations and they are at higher risk for chronic lung disease.

Some authors recently tried to administer CCSP to preterm neonates. CCSP is a natural inhibitor of sPLA2 in the lung [21,22]. This drug has been given endotracheally together with surfactant [21] achieving a significant reduction in lung tissue inflammation. Similar results in terms of inflammatory markers and lung function have been obtained in animal models of iRDS and MAS [23-25].

Other authors have proposed the same approach with endotracheally administered budesonide, vehicled by surfactant [26]. Budesonide inhibits sPLA2 and has been associated with a decrease in the release of sPLA2-induced pro-inflammatory cytokines [27]. Surfactant is the cornerstone of iRDS therapy and the sPLA2 inhibition could theoretically protect it, reducing the need for repeated doses and improving the long-term respiratory outcome.

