## Methods and design

### Study hypothesis and purposes

Available data allow hypothesizing a role for sPLA2 or its modulators in the pathogenesis, in the clinical severity and in the development of complications of the above mentioned types of lung injury. Our aim is to clarify such role, in order to better understand whether or not sPLA2 therapeutic inhibition might be a helpful strategy. To do that, we are planning to:

1. Identify the exact subtype(s) of sPLA2 produced and secreted into the alveoli during post-neonatal ARDS-ALI, MAS, iRDS and IRRF. This is important to know because sPLA2 inhibitors may have a different specificity for the various enzyme subtypes. In animal models, distinct sPLA2 subtypes have been associated to lung dysfunction [1,48-50].

2. Study the main modulators of sPLA2 expression and activity (TNFα, CCSP, SP-A and IL1). This will allow identification of possible pathway imbalances and eventually new therapeutic targets.

3. Clarify what happen to sPLA2 and its pathway when exogenous surfactant is administered, as it usually occurs to preterm neonates. This will allow to understand if there is a link between sPLA2 activity/overexpression, the repeated need for surfactant and BPD occurrence.

4. Clarify if there is a genetic predisposition due to different sPLA2 genes polymorphisms which could lead to more severe clinical pictures in iRDS, ARDS, MAS or IRRF or to a long term negative outcome.

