#### 1) clinical phase

##### Enrolment

The following group of patients will be identified: iRDS, IRRF, MAS, ARDS-ALI. To be enrolled in a group babies must fulfil all the following inclusion criteria:

A. Preterm neonates (gestational age ≤ 37 sett) with iRDS

*C-Reactive protein (CRP) < 10 mg/L or procalcitonin (PCT) < 0.6 ng/mL in the first 72 hours of life; Chest-X-rays typical for iRDS; no clinical signs of sepsis; need for mechanical ventilation*.

B. Infants and neonates with IRRF (regardless of the age)

***B1. Early IRRF. Neonates from mother with vaginal or urine positive cultures***. *Respiratory distress signs and CRP > 10 mg/L *[52]*or PCT > 0.6 ng/mL *[53]*in the first 72 hours of life; clinical signs of sepsis or blood/BALF positive culture; need for mechanical ventilation*.

***B2. Late IRRF***. *Neonates with respiratory distress signs beyond the first 72 hours of life or infants, irrespectively of the age and CRP > 10 mg/L *[52]*or PCT > 0.6 ng/mL *[53]; *clinical signs of sepsis or blood/BALF positive culture; need for mechanical ventilation*.

C. Neonates with MAS

*Neonates with meconium stained and thick amniotic fluid who required broncho-aspiration following Neonatal Resuscitation Program guidelines*[54]. *Continuous need for mechanical ventilation at 15 minutes of life. Chest-X rays typical for MAS*.

**D. Infants with ARDS-ALI **[55]

*Infants beyond neonatal age (> 30 days of life) and < 1 year of age under mechanical ventilation and having PaO_2_/FiO_2 _ratio < 200 (ARDS) or < 300 (ALI), chest-X rays typical for ARDS-ALI, acute onset of the respiratory distress and no cardiogenic oedema/increase in left atrial pressure*.

A control group has also been previewed, as follows:

E. Infants and neonates without respiratory diseases (NLD: No lung disease)

*Patients ventilated for non-pulmonary reasons (e.g.: anaesthesia, central nervous system diseases), PaO_2_/FiO_2 _ratio > 300 or FiO_2 _= 0.21, negative CRP and PCT, normal chest-X rays and chest clinical examination*.

A careful revision of the clinical characteristics will be done for each patient at the moment of discharge (or death). This will be done in each centre to ensure the appropriateness of diagnosis and internal validity.

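### With about 10-12 BPD cases expected at the cited 20% rate, Firth's penalised-likelihood logistic regression is a safer and nearly free choice for BPD and other sparse binary outcomes

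*Protocol article*

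**What the plan says.** Study hypothesis and purposes sets two aims that involve a binary long-term outcome. Aim 3 looks for "a link between sPLA2 activity/overexpression, the repeated need for surfactant and BPD occurrence". Aim 4 asks about sPLA2 polymorphisms "which could lead to more severe clinical pictures in iRDS, ARDS, MAS or IRRF or to a long term negative outcome". BPD is recorded for preterm neonates under the NICHD definition (Data to be registered in the intensive care units), and 15 SNPs are to be genotyped (sPLA2 genetics).

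Statistics and sample size plans "50-60 preterm infants affected by iRDS, with at least 20 receiving a second surfactant dose" as a convenience sample. For genotype: "The association between genotypes and clinical data will be tested with χ^2^- or Fisher test and then with logistic regression or analysis of co-variance", with the choice left to what suits the data. For laboratory measures, significant univariate results may, if needed, go on to a multivariate analysis whose type is not named. Power was checked only for correlations of sPLA2 activity with respiratory compliance and with PaO2/FiO2.

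The only BPD rate in the document is in the background section sPLA2 and iRDS: "with 20% of the surviving preterm babies affected by BPD".

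**The concern.** The precision and stability of a logistic model depend on the number of infants in the rarer outcome category, not on the total enrolled. At the cited rate that number is small in the iRDS group. Maximum-likelihood log odds ratios are then biased away from zero. If no BPD case carries a given minor allele, the data separate and no finite estimate exists.

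The study is meant to inform whether sPLA2 inhibition is worth pursuing. Overstated odds ratios, or SNPs dropped because the fit failed, would make that evidence less reliable. The same applies to other binary outcomes in the ARDS and IRRF groups: with 20 infants, the rarer category can hold at most 10.

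**Working it through.** **1. The plan's own figure.** With Fisher's z, power = Φ(atanh(r)·√(n−3) − 1.96), two-sided α 0.05.
- r = 0.6, n = 20: 0.693 × 4.123 − 1.96 = 0.90, power 81.5%.
- r = 0.85, n = 20: 1.256 × 4.123 − 1.96 = 3.22, power 99.9%.

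The stated power above 80% reproduces. It concerns two continuous correlations and says nothing about BPD.

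**2. Expected BPD cases.** Cases = N × rate.
- 20% (cited): 0.20 × 50 = 10; 0.20 × 60 = 12.
- 40% (assumed, for a sicker cohort): 20 to 24.
- 20% with 90% survival (assumed): 9 to 10.8.

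At 20%, the binomial chance of fewer than 10 cases is 44% with N = 50 and 21% with N = 60.

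**3. Events per model term.** With 10 or 12 cases: 10 or 12 for one term, 5 or 6 for two, 3.3 or 4 for three, 2 or 2.4 for five.

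**4. Bias in the sPLA2 odds ratio.** Simulation, 1,000 runs per row, 20% BPD. Assumed, not from the document: true odds ratio 2 per SD for sPLA2 and 1.5 per SD for each other term. Terms include sPLA2. Mean OR is the exponential of the mean log odds ratio; maximum-likelihood (ML) means are over fits that converged.

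| N | Terms | ML mean OR | Log-OR inflation | ML 97.5th percentile OR | Firth mean OR |
|---|---|---|---|---|---|
| 50 | 1 | 2.17 | 12% | 6.0 | 2.01 |
| 50 | 2 | 2.20 | 14% | 7.1 | 1.98 |
| 50 | 3 | 2.25 | 17% | 8.6 | 1.98 |
| 50 | 5 | 2.67 | 41% | 20.2 | 2.05 |
| 60 | 1 | 2.12 | 8% | 5.3 | 1.99 |
| 60 | 2 | 2.20 | 14% | 6.4 | 2.02 |
| 60 | 3 | 2.17 | 12% | 6.3 | 1.96 |
| 60 | 5 | 2.42 | 27% | 9.0 | 2.03 |

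Ordinary fits failed in 0.4% of runs or fewer in every row. At a 40% rate and N = 60, inflation falls to 7%, 11% and 17% with one, three and five terms.

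**5. Separation with a SNP in the model.** A hand check: with minor-allele frequency q, Hardy-Weinberg proportions and no association, the chance that none of m cases carries the minor allele is (1−q)^(2m).
- q = 0.3, m = 10: 0.7^20 = 0.08%.
- q = 0.1: 0.9^20 = 12% (m = 10); 0.9^24 = 8% (m = 12).
- q = 0.05: 0.95^20 = 36% (m = 10); 0.95^24 = 29% (m = 12).

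If the allele raises risk, cases carry it more often and these figures fall. Two-term simulations give ordinary-fit failure of about 6-7% at q = 0.1 and 22-28% at q = 0.05. Runs coded by carriage, with an assumed carrier odds ratio of 2, agree in pattern: 0.5-1.1% failure at 40% carriers, 16-23% at 10% carriers (q near 0.05, since 1 − 0.95² = 0.0975) and 46-55% at 5%. Firth's estimate stays finite under separation, provided the sample contains at least one carrier.

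**The case against.** Much of the case on the other side stands.

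- **The 20% is not the plan's assumption.** It describes surviving preterm babies in general. Every infant in this group is ventilated (Enrolment: "Chest-X-rays typical for iRDS; no clinical signs of sepsis; need for mechanical ventilation"), and at least 20 are to receive a second surfactant dose. The rate could be well above 20%, while deaths could lower the count. This stands, which is why the range is shown.
- **No ordinary multivariable model for BPD is fixed.** Logistic regression is named only for genotype against clinical data, as one option. For sPLA2 the multivariate step is conditional and its type is not given. No covariates are listed, and such details may sit in an analysis plan not shown. This stands too: the bias is conditional on ordinary maximum likelihood being used.
- **Fisher's test comes first** and remains valid in sparse genotype tables. True, but it gives no adjusted estimate, and the regression follows it.
- **No power is claimed for BPD.** Correct; the power statement is confined to the two correlations and is not wrong.
- **Imprecision outweighs bias.** In models that also contained a SNP, gestational age and re-dosing, the root mean square error of the log odds ratio was 0.65-0.82 with ordinary fits and still 0.50-0.58 with Firth. Firth helps but cannot supply missing events.

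What remains is that logistic regression is the named route to genotype-outcome associations, the sample size is set here, and a better-behaved version of the same method costs almost nothing.

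**Conclusion.** The point holds as a low-cost improvement. At the cited rate about 10-12 BPD cases are expected, or 20-24 at an assumed 40%. If ordinary logistic regression is used, the log odds ratio for sPLA2 is inflated by roughly 8-17% with one to three terms and 27-41% with five. Fits for uncommon SNPs fail in a noticeable share of runs. The effect sizes and allele frequencies behind these figures are assumptions; the document gives none for its 15 SNPs.

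A reader might infer that the adjusted odds ratios will inevitably be inflated or not estimable. The document does not support that: it commits to no particular model for BPD, and with few terms and a common genotype the bias is modest and failure rare. Nor does any passage make adjusted BPD odds ratios the deciding evidence on sPLA2 inhibition.

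**What to change.** In Statistics and sample size, state that BPD and other binary outcomes with few events will be analysed with Firth's penalised-likelihood logistic regression and profile-likelihood intervals, with genotype entered as one additive allele-count term. Describe the BPD analyses as exploratory estimation. Keep the covariate set small and prespecified. It need not be limited to gestational age, because aim 3 names repeated surfactant need as part of the question.

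The cost is a few sentences, slightly less familiar software and a small shrinkage of the estimates. No extra patients or data are needed. Firth's method does not correct for carrying forward only significant univariate results, which is a further reason to fix the model in advance.

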##### sPLA2 genetics

sPLA2-IIA [HGNC:9031], -V [HGNC:9038] and -X [HGNC:9029] genes polymorphisms will be studied in the patients' leukocytes. We found 15 single nucleotide polymorphisms (SNP) for these genes. These polymorphisms were searched in the dbSNP (http://www.ncbi.nlm.nih.gov/SNP/), JSNP (http://snp.ims.u-tokyo.ac.jp), GenBank at the NCBI (http://www.genbank.com) and Applied Biosystems genotyping databases (http://www.appliedbiosystems.com), as well as in a previous study linking them to coronary artery disease [47]. Analysis of genetic polymorphisms SNP genotyping will be performed by TaqMan allelic discrimination assay [65]. Polymerase chain reaction will be performed with specific primers at concentrations of 900 nM. Fluorescence data files from each plate were analyzed by a specific software. In order to verify the correct genotype assignment, we will randomly analyse some of the above screened samples by means of genetic sequencing (BigDye terminator technique).

All laboratory procedures will be carried out respecting safety regulations and bench investigators will be blinded to the patients' group of origin and to their clinical data. To accomplish this blindness, before starting the bench phase all vials will be re-labelled with a new code and only the project coordinators will be aware of the new code.

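### Hardy-Weinberg equilibrium is tested only by chi-square, which gives misleading p-values for rare alleles in groups of 10 to 60 infants; an exact test should replace it

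*Protocol article*

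**What the plan says.** All references are to the protocol article.

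- **sPLA2 genetics** gives the number of loci: "We found 15 single nucleotide polymorphisms (SNP) for these genes".
- **Statistics and sample size** names one method for equilibrium, a chi-square "test for the Hardy-Weinberg equilibrium of alleles at the individual loci". It does not say whether the test is run per group or pooled, or what follows from a significant result.
- The same section continues: "The association between genotypes and clinical data will be tested with" a chi-square or Fisher test, "and then with logistic regression or analysis of co-variance, as appropriate". Neither step states how genotype is coded.
- Planned numbers are "50-60 preterm infants affected by iRDS, with at least 20 receiving a second surfactant dose" and "for ARDS and IRRF groups 20 patients will be also convenient, while 10 control neonates or infants will be considered".

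The article gives no allele frequencies, genetic effect sizes or genetic power figure.

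**The concern.** The chi-square approximation needs reasonable expected counts. For a SNP, the smallest expected count is that of the rare homozygotes, n·q² for minor-allele frequency q. In groups of 10 to 60 this is well below 1 for a rare allele, so one infant can dominate the statistic. Offering Fisher for association suggests that sparse tables were foreseen there, yet the equilibrium test has no exact counterpart.

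At stake is how a rare SNP is read. A small equilibrium p-value usually raises doubt about genotyping or sampling. Here it could arise from an unremarkable sample.

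A second, smaller matter is that the association test names no genetic model. With few rare homozygotes, power depends on whether genotype enters as three unordered classes or as an allele count.

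**Working it through.** **The plan's own figure.** The only power statement concerns correlations: "Given α-error of 0.05 and a correlation coefficient" of at least 0.6 or 0.85, "respectively, the power resulted > 80% in both cases". By Fisher's z, power = Φ(atanh(r)·√(n−3) − 1.96), two-sided. At n = 20:
- r = 0.6: 0.693 × 4.123 − 1.96 = 0.90, power 81.5%.
- r = 0.85: 1.256 × 4.123 − 1.96 = 3.22, power 99.9%.

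The figure reproduces at n = 20, but it says nothing about the genetic tests.

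**Hardy-Weinberg, one table in full.** Take n = 60 with 56 common homozygotes, 3 heterozygotes and 1 rare homozygote. Then q = (3 + 2)/120 = 0.0417.
- Expected counts: 60(1−q)² = 55.10, 120q(1−q) = 4.79, 60q² = 0.104.
- Chi-square = 0.896²/55.10 + 1.792²/4.79 + 0.896²/0.104 = 0.01 + 0.67 + 7.70 = 8.39 on 1 df, p = 0.0038. The single rare homozygote supplies 7.70 of the 8.39.
- Exact: given 5 minor alleles, the heterozygote count can be 5, 3 or 1. Relative probabilities are 1, (5·4/56)/4 = 0.0893, and 0.0893 × (3·2/(57·2))/4 = 0.00117. So p = (0.0893 + 0.00117)/1.0905 = 0.083.

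Under equilibrium, five minor alleles in 60 infants therefore give at least one rare homozygote about 8% of the time. The chi-square test reports 0.4%.

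**Other tables with one rare homozygote.** Counts are common homozygote/heterozygote/rare homozygote.

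| n | Counts | Allele frequency | Expected rare homozygotes | Chi-square p | Exact p |
|---|---|---|---|---|---|
| 10 | 9/0/1 | 0.10 | 0.10 | 0.002 | 0.053 |
| 20 | 18/1/1 | 0.075 | 0.11 | 0.004 | 0.077 |
| 20 | 17/2/1 | 0.10 | 0.20 | 0.047 | 0.152 |
| 20 | 16/3/1 | 0.125 | 0.31 | 0.160 | 0.246 |
| 60 | 57/2/1 | 0.033 | 0.07 | 0.0002 | 0.0502 |
| 60 | 56/3/1 | 0.042 | 0.10 | 0.004 | 0.083 |
| 60 | 55/4/1 | 0.05 | 0.15 | 0.021 | 0.123 |
| 60 | 54/5/1 | 0.058 | 0.20 | 0.061 | 0.169 |

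The 5% verdicts part only in a narrow band of rare alleles. Pooling moves the band without removing it. With 20 infants in each of ARDS and IRRF (an assumed reading), the stated groups total 100 to 110; at n = 110, 102/7/1 gives 0.047 against 0.157.

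**Overall error rate at the 5% level**, by full enumeration under equilibrium for allele frequencies 0.05 to 0.30:
- Chi-square: 3.6% to 6.0% at n = 20, 3.9% to 5.1% at n = 60.
- Exact: 0.8% to 1.7% at n = 20, 1.0% to 3.5% at n = 60.

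**Genotype coding.** The following were simulated, 4,000 runs per setting. Assumed, not in the article: binary outcome, baseline risk 25%, allele frequency 0.10, 0.30 or 0.45. Figures are power of the 1-df trend test minus power of the 2-df chi-square test, in percentage points.
- Additive effect, per-allele odds ratio 2 to 4: +0.5 to +15.3 at n = 20, +3.0 to +11.5 at n = 60.
- Dominant effect, carrier odds ratio 4: −3.9 to +3.6.
- Recessive effect, homozygote odds ratio 16: +0.2 to −22.6. The worst case is n = 60, frequency 0.30: 49.9% against 72.5%.

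**The case against.** **The chi-square test is not broken overall.** Its average error rate is close to 5%, nearer nominal than the exact test's. This stands. A reader might infer that the p-value is unusable wherever fewer than one rare homozygote is expected (q below 0.129 at n = 60, since 60q² = 1 there). The tables do not support that: 51/8/1 at n = 60 has 0.42 expected and gives 0.324 against 0.335. What survives is that the near-nominal average hides p-values several times too small at particular allele counts.

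**No harm follows in the document.** A reader might infer that a SNP failing the test would be dropped. The article sets no such rule, and it checks genotype assignment separately by sequencing randomly chosen samples. This also stands.

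**The association analysis may already use allele dose.** It is tempting to read the association sentence as an unordered three-class table that discards dose. The article does not say so. It states no coding and goes on to logistic regression or analysis of covariance, either of which could carry a 0/1/2 count. It does not clearly make the first test a gate to the second. Coding is also a detail that an article commonly leaves to the full plan, so its absence is not an error. The benefit of a trend test rests on an additive effect that the article neither states nor supports.

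**Conclusion.** The point holds for the Hardy-Weinberg test, and it is minor. The stated chi-square method can give p < 0.05 on the strength of one infant where the exact test does not reject. This happens at allele frequencies of about 0.03-0.05 at n = 60 and up to about 0.10 at n = 20. In the four discordant tables at n = 20 and n = 60 with exact p between 0.077 and 0.152, the chi-square p-value is too small by a factor of about 3 (0.152/0.047) to 22 (0.083/0.0038). These are properties of the tables and need no assumed effect. Whether any of the 15 SNPs is this rare cannot be told from the article.

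General inflation, loss of SNPs, and a planned analysis that ignores allele dose are not shown. On coding, only a suggestion remains. Its size, very roughly 1 to 15 points gained, depends on assumed additive effects, frequencies and baseline risk, and its sign reverses under a strong recessive effect.

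**What to change.** 1. Replace the chi-square Hardy-Weinberg test with the exact test at every locus, and say whether it is run per group or pooled. This changes wording only. The cost is a conservative test (true size about 1% to 3.5% at a nominal 5%), hence less power to detect real departures.
2. As an optional addition, state the genotype coding and report a 1-df test on 0/1/2 allele copies alongside the unordered genotype test, with the same coding choice carried into the regression step. Keep the genotype test, because the allele-count test can lose over 20 points under a strong recessive effect. The cost is one more test per SNP and outcome, so the roles of the two tests should be fixed before the data are seen.

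Neither change needs more patients, samples or assays.
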